### Ethical approval

This study protocol was approved by the Medical Ethical Committee of the Radboud university medical center on 9 August 2011 (registration number: 2011/318). The study conforms to Dutch law and privacy regulations and was judged not to involve human-subject research. This study is registered in the Dutch Trial Registry for clinical trials [45] (record number NTR3568). The participation of hospitals in the study is voluntary. The research team gave oral presentations and written information about the study to each hospital. Written consent has been obtained from all participating hospitals before randomization. Because outcome data are routinely collected by the hospitals and no personal identifiers are transmitted, individual consent of patients is not required. All data will be handled strictly confidential and published anonymously. Each participant is identified in the database with a study number.

### Trial status

Between May 2012 and June 2015, nine hospitals have been found willing to participate in this study. At the time of submission of the manuscript, no data cleaning or analysis has begun.

## Discussion

From the literature, we know that adherence to guidelines is too low [46] and because of this the safety of patients is at stake. This is not different for the guidelines on the perioperative process. Many potentially effective implementation strategies are available [20], but the understanding of whether and why a strategy is successful is still limited; some implementation strategies have been found to be invariably effective in some settings, but not in others [19]. The perioperative setting is an unexplored area with respect to implementation topics. Our study will provide a better understanding of guideline implementation within the perioperative care process. With this study, we hope to show that a tailored multifaceted implementation strategy will be as successful in the perioperative setting as in other settings [20]. This is important for the further implementation of the perioperative guidelines in all Dutch hospitals. To the best of our knowledge, this is the first study examining the effects of a multifaceted approach in the perioperative care setting. Knowledge on the effects of our multifaceted approach to implement the perioperative safety guidelines can be used to improve perioperative patient safety.

This study has several strengths and limitations. The major strength of this study is the randomized comparison made possible by the multicenter stepped wedge cluster randomized trial design. In fact, a parallel group cluster randomized trial was not feasible because of the large number of hospitals needed. A (individually) randomized, controlled trial was not possible as all Dutch hospitals have a legal obligation to implement the perioperative safety guidelines; temporarily postponing the implementation of the guidelines would have been unethical. Finally, non-randomized designs such as pre- and post-intervention evaluations are methodologically weaker as they tend to overestimate intervention effects. Another strength of our study is the use of a multifaceted approach consisting of in total 11 different activities, covering six interventions: education, audit and feedback, organizational interventions, team-directed interventions, reminders, as well as patient-mediated interventions, of which most have been shown to be effective in other studies [20,41,47-52]. Combinations of interventions may be more effective than single interventions in changing professional behavior, because a larger variety of barriers for change can be addressed [53]. The effectiveness of a combined strategy is determined by the effectiveness of the separate interventions that make up the strategy and the interaction of the different interventions, which can increase or reduce the total effect. The effect of a combined intervention does not necessarily equal the sum of the effects of the single interventions that comprise it. Different interventions can support each other, so the total effect may be larger than the effects of the interventions separately [53]. However, no specific combination provides a guarantee for success [53]. It seems plausible that combined interventions are only more effective than a single intervention if they address barriers and facilitators that are actually related to professional performance. This emphasizes the importance of a careful documentation of the most important barriers to improvement and the systematic development of implementation strategies as in our study, which is preferred over intuitively selected strategies [53,54]. A multifaceted implementation strategy with activities that are not carefully related to the relevant factors and needs of the target group is an unfocused intervention and likely not effective [53].

The generalizability of the findings will be high because the study is carried out in a large, heterogeneous sample of nine hospitals across the country. A further strength of this study is the wide scope; we perform measurements at the cluster level and the level of their individual members, i.e., care providers and patients. A questionnaire is sent to the key disciplines to explore all relevant barriers and facilitators to guideline adherence and opportunities for improvement. A better understanding of the barriers and facilitators and a strategy tailored to local circumstances will enhance the implementation of the perioperative guidelines like already mentioned [55,53]. We also carry out a process evaluation to analyze the mechanisms and processes responsible for the outcomes of the effect evaluation; a causal relationship between implementation activities and change in outcomes is difficult to identify because of the presence of confounding factors, like local hospital initiatives to improve patient safety. In case of a multifaceted implementation strategy, the process evaluation is especially important to specify which intervention was most effective [53]. Insight into the implementation process is also relevant for other hospitals that can benefit from the lessons learned. To improve the internal validity, the following actions will be undertaken. To reduce selection bias, the first 50 patients that meet the inclusion criteria are selected from the hospital databases in all hospitals at each measurement point. A possible limitation of the survey investigations is response bias, which will be minimized by sending reminders. Information bias is reduced by having the same researchers (YE and GB) checking the data from the hospital registries and medical records. An independent researcher checks the data entries. An independent statistician will check the analyses. To prevent confounding bias, we study potentially confounding determinants, such as team climate and patient safety culture. To prevent publication bias, the study has been registered in the Dutch register for clinical trials. Additionally, we have installed an external advisory board with the special tasks of checking the design and the integrity of the study and giving feedback.

With respect to the limitations of the study, the power of the stepped wedge cluster randomized trial design decreases if the treatment gradually reaches its expected effect after one or more time intervals after the intervention [22]. The greater the delay in the intervention effect, the greater the loss of power. This can be a problem in the third group of hospitals as the effect measurement is conducted immediately after the implementation phase (the last group starts with the implementation activities after T2). It is therefore important to make the time intervals sufficiently long so that the full intervention effect is realized in a single interval. The power can also be partly, but not completely, restored by adding additional measurement periods onto the end of the trial. Another limitation of this study is the costs of the frequent data collection. If the necessary data are not easy to collect and time-consuming, the cost of data collection is substantial. A further limitation is due to the fact that our sample size is calculated for the primary outcome measure. Power may be too low to draw conclusions about the effect of guideline adherence on perioperative patient safety. Blinding of the intervention is not possible as the trial is designed to evaluate an implementation intervention to change professional behavior in the real hospital setting. Outcomes assessment was not blind either, but as indicators are rather objective (e.g., is a protocol for anticoagulant use available or not), it is unlikely that they are influenced by the assessment.

Overall, knowledge of the results of this study will improve the implementation success of the perioperative guidelines. It is expected that better adherence to the perioperative safety guidelines will improve the safety of perioperative care.

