## Methods/design

### Study design

Implementation of Perioperative Safety Guidelines (in Dutch: Implementatie Richtlijnen Operatieve Veiligheid (IMPROVE)) is a multicenter study in nine hospitals using an one-way (unidirectional) cross-over cluster trial design (i.e., the clusters cross over in one direction only, from control to intervention) where each participating cluster receives both intervention and control treatments consecutively, in separate periods.

A stepped wedge design is a sequential roll-out of an intervention (here: the multifaceted implementation strategy) to participants (individuals or clusters of individuals, here: groups of hospitals) over a number of time periods. All groups (hence all hospitals) start with the control situation (no IMPROVE implementation activities) at the beginning of the study. At each time point, a new group of three hospitals crosses over from the control situation to the implementation situation. Good balance of hospital characteristics (e.g., hospital type and geographical location) over the groups (of three hospitals) was achieved by matching. Each group will start the implementation phase of 4 months at a different time point, directly after one of the measurements (T0, T1, T2). The time point a group crosses over is randomized (over the groups). Randomization was computer generated by an independent statistician when recruitment of clusters was complete (Additional file 1). By the end of the study, all groups (hence all hospitals) will have received the IMPROVE implementation strategy. The intervention is never removed once it has been implemented, at least over the course of the trial.

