In our protocol, hospitals cross over from control to implementation period at three time points (Table 1). A stepped wedge design incorporates data collection in all hospitals at each time point [21,22]. The first time point corresponds to a baseline measurement where none of the hospitals have received the intervention of interest (i.e., multifaceted implementation approach). After the baseline measurement, the first group of hospitals receives the implementation strategy. After the second measurement, the next group of hospitals receives the implementation strategy, and at the third time point, the final group switches from usual care to the implementation phase, so that finally, all included hospitals have received the implementation activities. In this way, comparisons within hospitals and between hospitals will be available, making the design powerful.

**Table 1 Tab1:** **Stepped wedge design with four steps in which ‘C’ represents the control situation and ‘I’ represents the intervention phase**

**Group**	**Measurement**			
	**T0**	**T1**	**T2**	**T3**
**1**	C	I	I	I
**2**	C	C	I	I
**3**	C	C	C	I

In this study, nine hospitals are assigned into three groups of three hospitals. Data collection runs parallel for each hospital. At baseline measurement (T0), all primary and secondary outcomes will be measured per patient (*N* = 50) per hospital. In the interval between T0 and T1, implementation activities will take place in the first group of three hospitals. After the second measurement (T1), the second group of three hospitals crosses over to the intervention phase, while implementation activities continue in the first group and so on. At the final measurement (T3), all hospitals will be in the intervention phase (see Table 1).

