### The intervention

The intervention consists of a multifaceted implementation strategy directed at the cluster. Each group of hospitals will be exposed to the intervention for 4 months. The content of the multifaceted approach is based on 1) scientific literature (systematic review of interventions by Grimshaw et al. [20,26]); 2) expert opinion: prioritizing implementation activities by 24 clinical and implementation experts (RAND modified Delphi method); 3) knowledge and experience of the IMPROVE team regarding the feasibility of the interventions (estimated costs, effort, and time for the hospitals as well as the implementation team). This resulted in a standard package including five activities (Table 2): 1. small educational meetings, 2. audit and feedback (based on local indicator scores and benchmarking, results of surveys on team climate and safety culture, and barriers), 3. structured observation rounds with feedback, 4. integration of the guidelines in local activities and processes, and 5. the use of patient safety cards. A set of six additional activities are offered optional: 1. personal information letter in the mailbox, 2. exchange platform for sharing information between hospitals within a group, 3. scan of the total perioperative process, 4. posters showing details of the perioperative care process, 5. reminder flashes via e-mail, and 6. team training.

**Table 2 Tab2:** **Description of the content of the implementation activities in the IMPROVE standard and additional packages**

**Implementation activities**	**Description**

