### Outcome measures

Several outcomes are measured at the hospital (i.e., the cluster) and the patient levels (Table 3). The primary outcome measure is guideline adherence according to the PSIs as defined in the national indicator set. This set comprises nine indicators on the processes and structures of care [18]. Secondary (patient) outcomes are in-hospital complications (with particular attention to postoperative wound infections) and hospital mortality, as well as length of hospital stay (LoHS), unscheduled transfer to the intensive care unit (ICU), non-elective hospital readmission, and unplanned reoperation, which are derived from a maximum period of 30 days after the initial surgery.

**Table 3 Tab3:** **Methods and instruments for measuring the effects of a multifaceted implementation strategy to implement the Dutch national perioperative safety guidelines**

**Outcome variable**	**Data source (type of measurement)**	**Frequency of measurement and sample size per measurement**	**Moment of measurement**	**Unit of analysis**
**Primary outcome** (guideline adherence measured by an indicator set of nine process and structure indicators)				
Completion of the total STOP bundle (seven separate stop moments in the perioperative care process), % patients	Retrospective patient record review in the hospital information systems	4 (T0 (before), T1, T2, T3 (after) measurement) *N* = 1,800	−3 months, +4 months, +11 months and +18 months	Patient
Availability of a protocol on antibiotic use	Short questionnaire on the underlying items of the structure indicators	4 (T0 (before), T1, T2, T3 (after) measurement) *N* = 1	−3 months, +4 months, +11 months and +18 months	Hospital
Timely administration of antibiotic prophylaxis, % patients	Retrospective patient record review in the hospital information systems	4 (T0 (before), T1, T2, T3 (after) measurement) *N* = 1,800	−3 months, +4 months, +11 months and +18 months	Patient
Availability of a protocol on anticoagulant use	Short questionnaire on the underlying items of the structure indicators	4 (T0 (before), T1, T2, T3 (after) measurement) *N* = 1	−3 months, +4 months, +11 months and +18 months	Hospital
Availability of a protocol on responsibilities regarding maintenance of medical equipment	Short questionnaire on the underlying items of the structure indicators	4 (T0 (before), T1, T2, T3 (after) measurement) *N* = 1	−3 months, +4 months, +11 months and +18 months	Hospital

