### Analysis

After each measurement period, data are manually checked to identify out-of-range answers, inconsistent or missing data. Because of the hierarchical design (patients nested within hospitals), multilevel linear and logistic regression analysis will be used to compare the outcomes between treatment groups, with age, sex, the American Society of Anesthesiologists (ASA) physical status classification, and socioeconomic status (SES) as covariates. The ASA physical status classification is a five-point scale ranging from ASA 1 (healthy patient) to ASA 5 (moribund patient not expected to survive without surgery, e.g., a patient with a ruptured aortic aneurysm) [41]. Time will be included as fixed effect [22]. The association between guideline adherence and patient outcomes will also be analyzed to determine whether better adherence leads to better patient outcomes. We will use SPSS version 20.0 for data analysis. Significance for all analyses will be set at *P* < 0.05.

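### The implied single intervention effect is biased if the effect grows or wanes after roll-out; the Discussion treats a gradual effect as only a power loss, mainly for the third group

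*Protocol article*

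**What the plan says.** The Study design section states that "nine hospitals are assigned into three groups of three hospitals" and that "hospitals cross over from control to implementation period at three time points". Table 1 gives the pattern C-I-I-I, C-C-I-I and C-C-C-I. On timing: "Each group will start the implementation phase of 4 months at a different time point, directly after one of the measurements". Table 3 puts baseline at −3 months and the later measurements at +"4 months, +11 months and +18 months".

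The Analysis section plans multilevel linear and logistic regression comparing treatment groups, and adds: "Time will be included as fixed effect". It names no term for time since roll-out. The Power calculation section uses the Hussey-Hughes formula. It says treatment delay ought to be allowed for, but lists no delay among its assumptions.

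The limitations part of the Discussion raises gradual onset itself. It describes the consequence as lost power and continues: "This can be a problem in the third group of hospitals as the effect measurement is conducted immediately after the implementation phase". It recommends intervals long enough for the whole effect to appear within one of them, and mentions extra measurements at the end as a partial way to restore power.

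On what follows the 4-month phase, The intervention section says "Each group of hospitals will be exposed to the intervention for 4 months", while Study design says that the second group crosses over "while implementation activities continue in the first group and so on". Study design also says the intervention is not withdrawn during the trial.

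**The concern.** A single intervention indicator is safe only if the effect is the same at every measurement after roll-out. In this design, hospitals that have already crossed over serve as comparators for those crossing over later. If the effect in the earlier hospitals is still changing, that change enters the comparison with the wrong sign. The coefficient is then not an average of the real effects, and adding patients does not help.

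A strategy that works slowly could be reported as weak or ineffective, and one that fades could be overstated. The Discussion foresees a gradual effect but tells the reader to expect only less power, chiefly in one group.

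**Working it through.** **Lags.** Measurements are 7 months apart and roll-out takes 4. If each measurement occupies about 3 months, which fits the Discussion's statement that measurement follows directly on the phase, group 1 is observed about 0, 7 and 14 months after roll-out, group 2 at 0 and 7, and group 3 at 0. If measurement were instantaneous the lags would be 3, 10 and 17 months. The weights below depend only on the order, so they are the same either way. In both cases the first lag is identical in all three groups.

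**Inputs from the protocol.** I = 9 hospitals, T = 4 measurements, 50 patients per hospital and measurement, 50% rising to 65%, alpha 0.05, ICC 0.1 to 0.3. My assumptions: two-sided test, normal reference, total variance 0.25, ICC as a share of total variance.

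**The plan's own figure first.** The Hussey-Hughes variance is

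Var = Iσ²(σ² + Tτ²) / [(IU − W)σ² + (U² + ITU − TW − IV)τ²].

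- U = 18 intervention cells.
- W = 0² + 3² + 6² + 9² = 126.
- V = 3×(3² + 2² + 1²) = 42.
- IU − W = 162 − 126 = 36.
- U² + ITU − TW − IV = 324 + 648 − 504 − 378 = 90.

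At ICC 0.1, σ² = 0.9×0.25/50 = 0.0045 and τ² = 0.025. Var = 9×0.0045×0.1045 / (36×0.0045 + 90×0.025) = 0.004232/2.412 = 0.001755, so SE = 0.0419. Power = Φ(0.15/0.0419 − 1.96) = 0.947.

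At ICC 0.3, σ² = 0.0035 and τ² = 0.075. Var = 0.009560/6.876 = 0.001390, SE = 0.0373 and power is 0.980. The stated power of at least 0.85 is met if the effect is constant.

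**What the single coefficient estimates.** Generalised least squares on the 9×4 hospital-period means, with fixed period effects and a random hospital effect, gives these weights at ICC 0.1 (summed over the three hospitals of a group):

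| Group | T0 | T1 | T2 | T3 |
|---|---|---|---|---|
| 1 | −0.28 | 0.50 | 0.11 | −0.28 |
| 2 | 0.00 | −0.39 | 0.39 | 0.00 |
| 3 | 0.28 | −0.11 | −0.50 | 0.28 |

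Collecting the intervention cells by time since roll-out:

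- First: 0.50 + 0.39 + 0.28 = 1.17.
- Second: 0.11 + 0.00 = 0.11.
- Third: −0.28.

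At ICC 0.3 the weights are 1.192, 0.103 and −0.295. They sum to 1.

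**Direction of the bias.** Because the weights sum to 1, expected estimate − e1 = w2(e2 − e1) + w3(e3 − e1). If e1 ≤ e2 ≤ e3, this is at most (w2 + w3)(e2 − e1), which is −0.17(e2 − e1) at ICC 0.1. A rising effect is therefore expected to be estimated below its smallest value. By symmetry, a falling one is estimated above its largest.

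| True effects (points) | Expected estimate, ICC 0.1 / 0.3 |
|---|---|
| 7.5, 15, 15 | 6.2 / 6.1 |
| 5, 10, 15 | 2.8 / 2.6 |
| 0, 15, 15 | −2.6 / −2.9 |
| 15, 7.5, 7.5 | 16.3 / 16.4 |
| 10, 15, 10 | 10.5 / 10.5 |

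Example, first row at ICC 0.1: 1.170×7.5 + 0.110×15 − 0.280×15 = 6.2. Its power is Φ(0.0623/0.0419 − 1.96) = 0.32. At ICC 0.3 it is 0.37, or 0.38 with variance 0.575×0.425. For 5, 10, 15 power is about 0.10.

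**Logistic check.** In 400 simulated trials per scenario with hospital fixed effects, true log-odds effects of 0.20, 0.41 and 0.62 gave about 0.10. The reverse order gave 0.71 to 0.72, and a constant 0.62 gave 0.62 to 0.63.

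**Extra measurements at the end.** One added period at ICC 0.1 gives weights 1.06, 0.35, −0.20 and −0.20. The bias shrinks but stays.

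**The case against.** **The constant effect is inferred.** The article never uses those words, and a statistical analysis plan that is not shown might add an exposure-time term. This is fair, so the absence of such a term is not the finding. What stands is the Discussion's own statement about what a gradual effect does, which is incomplete in print.

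**The authors saw the condition.** Asking for intervals long enough to capture the full effect is in substance the condition for a constant effect. But it is offered to protect power, and the text does not say that the estimate is wrong when the condition fails.

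**Size.** In two-level profiles the estimate misses the range by 17 to 19% of the gap between the two effects. That is 1.3 to 1.4 points in the 7.5-to-15 example, about a third of one SE, so the coefficient roughly tracks the first-measurement effect. True, but it then sits well below the later 15 points, and steady growth does worse.

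**Three stronger readings are tempting and not supported.**

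- A reader might infer that the estimate always falls outside every true effect. It need not: 10, 15, 10 gives 10.5, inside the range. The statement also concerns the expected estimate; a single trial adds an SE of about 4 points.
- A reader might infer that two terms, first versus later, remove the bias while keeping 0.85 power. They remove it only if the effect is flat from the second measurement after roll-out. Effects of 5, 10, 15 give 3.6 to 3.7 and 8.8 to 9.0, averaging 6.2 to 6.3 against a true mean of 10. Power for the two-term average at ICC 0.1 is 0.842 with variance 0.25 and 0.850 with 0.575×0.425.
- A reader might infer that the protocol flatly contradicts itself on whether activities stop. A 4-month phase followed by further activity is a possible joint reading, given that the intervention is not withdrawn. The wording needs reconciling; it does not prove waning or growth.

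**Conclusion.** The point holds in this form. Under the model the article implies, a steadily growing effect is expected to be estimated below its smallest true value and a waning one above its largest, across the protocol's whole ICC range. Halved onset (7.5, 15, 15) gives 6.1 to 6.2 points with power 0.32 to 0.38; fading (15, 7.5, 7.5) gives 16.3 to 16.4. Non-monotone profiles can fall inside the range, and a truly constant effect is estimated correctly.

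The Discussion is therefore wrong to present a gradual effect as only a loss of power and as particular to the third group. It shifts the estimate, and the first lag is common to all groups.

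This rests on the single-effect model inferred above, equal cluster sizes and a random hospital intercept. The pattern persists at ICC 0.06 and 0.01 and disappears only at ICC 0, where the weights are 0.75, 0.25 and 0. With a cluster autocorrelation of 0.8 to 0.9 (my assumption) the first weight stays at 1.13 to 1.17 and the third at −0.25 to −0.28. The documents do not show that the effect will change over time; the Discussion itself treats it as possible.

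**What to change.** 1. Correct the limitations text: a gradual or fading effect biases the single estimate, this applies to all groups, and extra measurements at the end do not remove it.
2. State the constant-effect assumption in the Analysis section.
3. Beside the single-effect analysis, prespecify a model with separate effects for the first, second and third measurement since roll-out. Report each effect and their equally weighted average, and limit the conclusion if they differ.
4. Optionally report the two-term version (first versus later) as a more precise alternative, stating that it is unbiased only if the effect is flat from the second measurement onward.
5. Reconcile Study design and The intervention on whether activities continue after the 4-month phase.

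No new data are needed, and the article says analysis had not begun at submission. The cost is precision. With variance 0.25, the SE of the three-period average is 6.4 points at ICC 0.1 and 5.8 at ICC 0.3, against 4.2 and 3.7 for the single effect. Its power for a constant 15 points is about 0.65 to 0.74 over both variance conventions. The third effect rests on group 1 at T3 alone and has power of only about 0.35 to 0.41. The two-term average has power of about 0.84 to 0.91, so 0.85 is not assured at ICC 0.1. For that reason the added model is proposed beside the single-effect analysis, not in its place.
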